### Sample size

The expected discontinuation efficacy rate for the sham acupuncture group in the sample size calculation was derived from a randomized controlled trial that enrolled 144 long-term benzodiazepine users (21). However, this trial yielded a negative result, which might be attributable to the simultaneous inclusion of both BZDs and NBZDs in the study medication (22). Therefore, only the sham acupuncture group discontinuation rate of 10.83% was adopted from that trial, while the expected successful discontinuation rate for the acupuncture group was based on our pilot study.

A pilot study was conducted at our center prior to the main trial to assess the feasibility of the intervention and to obtain preliminary estimates of effect size. Ten eligible patients with chronic insomnia disorder who had used NBZDs regularly for >6 months received electroacupuncture (three times per week for 6 weeks) combined with the standardized 6-week NBZD tapering protocol (25% dose reduction every week). The successful discontinuation rate was 50.00% (5/10). No serious adverse events were reported. Detailed pilot study results are provided in Supplementary Appendix S2.

Based on expected outcomes and relevant published literature (21), this study hypothesized that after treatment, the discontinuation efficacy rates of NBZDs at 6-week post-treatment for the electroacupuncture group and sham needle and sham electroacupuncture group would be 50.00 and 10.83%, respectively. This study set *α* = 0.05 and 1-*β* = 0.90, employing a two-sided test with equal sample sizes between treatment and control groups. Referencing the sample size estimation formula for comparing efficacy rates between two groups from Sun Zhenqiu’s Medical Statistics, the calculation formula was as follows:

$$n=1641.4/{\left[\frac{\left(u_{\alpha }+u_{\beta }\right)}{\sin^{-1}\sqrt{P_{1}}-\sin^{-1}\sqrt{P_{2}}}\right]}^{2}$$

where 
$u_{\alpha }$
=1.96 (for 
α
=0.05, two-sided), 
$u_{\beta }$
=1.282 (for 
β
=0.10), P_1_ = 50.00%, and P_2_ = 10.83%. The calculation yields n = 31.7 ≈ 32 cases. Accounting for dropout rates, the clinically set dropout rate is 20%, resulting in a final sample size of 39 participants per group, totaling 78 participants across both groups.

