### Data management

Data collection will encompass three aspects: (1) Participants independently completing relevant scale assessments in the acupuncture treatment room. The assessment requires approximately half an hour. During this period, participants may consult dedicated assessment physicians regarding any questions. (2) Participants will complete sleep diaries at home throughout the study period under physician guidance.

This study will train data outcome assessors to enhance participant compliance, collect high-quality complete datasets, and facilitate follow-up completion. Dedicated personnel will perform data entry, receiving specialized training in data input procedures, coding protocols, and secure storage practices. Data analysts in this study will receive training in data evaluation and analysis methodologies. This study strictly safeguards participant privacy through the following primary measures: ① Requiring participants to provide only research-related personal information during the study process; ② Store data on designated computers with restricted access, ensuring the specific folders containing data are password-protected; ③ Only personnel involved in the research can access participants’ personal information, and this information will be destroyed upon completion of the study.

The full analysis set (FAS) will include all randomized participants who receive at least one treatment session and have at least one post-baseline assessment, consistent with the intention-to-treat principle. Missing outcome data will be handled using likelihood-based estimation within mixed-effects models under the missing-at-random assumption. Multiple imputation will be conducted as a sensitivity analysis. The safety set (SS) will include all participants who receive at least one treatment session. The pilot data and the main trial data will be pooled after completion of the main trial to conduct sensitivity analyses assessing the robustness of the conclusions.

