### Study limitations

Several limitations should be acknowledged. First, the generalizability of our findings may be constrained by the single-center design and the use of a standardized tapering protocol. As an early-stage exploratory study, the single-center design was intentionally adopted to maximize internal validity, minimize the heterogeneity and costs associated with multi-center trials, and enhance reproducibility, thereby laying the groundwork for future multi-center investigations. However, this design inevitably involved a relatively homogeneous and highly adherent patient population, which may introduce selection bias. Additionally, access to specialized acupuncturists and frequent monitoring—resources that are not universally available in routine clinical settings—further limits the applicability of our findings. Furthermore, while the standardized tapering protocol reduced performance bias, improved reproducibility, and provided a clear estimate of treatment efficacy, its rigidity may lead to suboptimal adherence in some patients and fails to account for real-world interpatient variability. Therefore, our results reflect efficacy under optimized conditions; the effectiveness of this intervention in heterogeneous, resource-limited, or less supervised settings may differ. Future pragmatic multi-center trials incorporating flexible, patient-centered tapering strategies are needed to establish broader applicability. Second, the single-blind design ensures participant blinding but does not permit blinding of treating acupuncturists, introducing the possibility of performance bias. This design was selected to preserve treatment fidelity while maintaining methodological rigor. Third, it must be acknowledged that the small sample size of the pilot study may have introduced uncertainty in the estimation of the effect size. Therefore, after completion of the main trial, the pilot data will be pooled with the main trial data to conduct sensitivity analyses assessing the robustness of the conclusions under different effect size assumptions. Furthermore, future multi-center, large-sample confirmatory trials are recommended to validate the findings of the present study. As a final note, although plausible neurobiological mechanisms are proposed, mechanistic pathways are not directly evaluated. Future studies incorporating neuroimaging, electrophysiological measures, or biomarker assessments would help clarify the underlying mechanisms of action.

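### Pooling the ten electroacupuncture-only pilot patients with the randomised trial gives a biased sensitivity analysis, favouring electroacupuncture whenever the trial's own electroacupuncture rate is below 50%

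*Protocol article*

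**What the plan says.** The Sample size section describes the pilot: "Ten eligible patients with chronic insomnia disorder who had used NBZDs regularly for >6 months received electroacupuncture", together with the same taper as in the main trial. It reports one discontinuation rate, 5/10 or 50.00%. It mentions no sham patients and no random allocation. The same section takes the planned electroacupuncture rate of 50.00% from this pilot and the planned sham rate of 10.83% from a published trial.

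The Data management section then commits to the pooling: "The pilot data and the main trial data will be pooled after completion of the main trial to conduct sensitivity analyses". The stated aim is to assess how robust the conclusions are. Study limitations repeats the plan as the answer to the pilot's small size: "the pilot data will be pooled with the main trial data to conduct sensitivity analyses". There the stated purpose is to see whether the conclusions hold when the assumed effect size is varied.

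The Data management section also defines the main efficacy set: "The full analysis set (FAS) will include all randomized participants who receive at least one treatment session". A post-baseline assessment is required as well. The pilot patients are outside that set, and the pooling is labelled a sensitivity analysis.

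**The concern.** A sensitivity analysis of a randomised comparison should change one assumption and leave the comparison itself intact. This one changes the comparison. It adds patients to one arm only, and those patients were not randomised against sham and had no sham procedure to be blinded against. Their outcome is already known, and it is the source of the effect the trial was sized to detect.

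The harm is to interpretation. If the randomised result is null or weak, a pooled analysis that reaches significance could be reported as evidence of robustness when the pilot's 5/10 has produced the difference.

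The pooling also does not do what Study limitations offers it for. The assumed effect size determined how many patients to recruit. It does not enter the comparison of observed outcomes, so adding the data that produced the 50% assumption does not test any other assumption.

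**Working it through.** **Inputs, all from the protocol article.** Pilot: 5/10 = 50.00%, electroacupuncture only (Sample size). Main trial: 39 per group (Sample size; Randomization). Planned sham rate 10.83%; two-sided α = 0.05 (Sample size). Dropout 20% (Sample size), so 39 × 0.8 = 31.2, about 31 per arm with outcomes.

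**Assumption.** The article gives no pooling method, so I take simple addition of the pilot to the electroacupuncture arm.

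**Step 1: composition.** Electroacupuncture 39 + 10 = 49, sham 39. The non-randomised share of the electroacupuncture arm is 10/49 = 20%.

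**Step 2: shift in the electroacupuncture rate.** If the trial's true electroacupuncture rate is p, the expected pooled rate is (39p + 5)/49. The shift is (39p + 5)/49 − p = 10(0.5 − p)/49.

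| p | pooled rate | shift (points) |
|---|---|---|
| 10.83% | 18.8% | +8.0 |
| 20% | 26.1% | +6.1 |
| 30% | 34.1% | +4.1 |
| 40% | 42.0% | +2.0 |
| 50% | 50.0% | 0 |
| 60% | 58.0% | −2.0 |

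The sign depends only on whether p is below or above the pilot's 50%.

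**Step 3: chance of a significant result favouring electroacupuncture when there is no true effect.** I enumerated exactly two independent binomial arms of 39 with a common rate. The fixed 5/10 was added to the electroacupuncture arm for the pooled version. Tests were the uncorrected chi-square and Fisher's exact test at two-sided 0.05, counting only rejections in favour of electroacupuncture.

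| common rate | chi-square, randomised only | chi-square, pooled | Fisher, randomised only | Fisher, pooled |
|---|---|---|---|---|
| 10.83% | 2.9% | 13.6% | 0.9% | 11.1% |
| 20% | 2.6% | 8.1% | 1.4% | 5.8% |
| 30% | 2.7% | 4.8% | 1.4% | 3.9% |
| 50% | 2.7% | 2.1% | 1.5% | 1.3% |

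With 31 per arm and 10.83% in both, the chi-square figures are 2.8% and 15.9%, and the Fisher figures 0.6% and 10.1%.

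**Step 4: single results in each direction.**
- 10/39 v 4/39 has p = 0.077 (chi-square) or 0.138 (Fisher). Pooled, 15/49 v 4/39 has p = 0.021 or 0.035. Significance is gained.
- 24/39 v 15/39 has p = 0.042 (chi-square). Pooled, 29/49 v 15/39 has p = 0.053. Significance is lost.

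**Step 5: would another pooling method rescue it?** In an analysis stratified by study, the pilot stratum has 10 electroacupuncture and 0 sham patients. Its Mantel–Haenszel weight is 10 × 0/10 = 0, so it adds nothing to the treatment comparison. Down-weighting each pilot patient by a factor w changes the shift to 10w(0.5 − p)/(39 + 10w). For example, w = 0.5 at p = 10.83% gives 5 × 0.3917/44 = 4.5 points. That is smaller than 8.0 but in the same direction.

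**The case against.** The best reply is that the pooling is only a sensitivity analysis, done after the main trial is complete, and that the full analysis set excludes the pilot. Study limitations also admits that the pilot was small and its estimate uncertain. This stands, and it limits the weight of the point. A reader might take 13.6% as the trial's false-positive rate. It is not: it is the chance that one secondary analysis, done by simple pooling, is significant when there is no effect.

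A second reply is that no pooling method is given, and that such detail may sit in an analysis plan that is not shown. That also stands, so simple pooling is stated here as an assumption. It does not remove the concern: stratification leaves the pilot with no weight, and down-weighting reduces the bias without removing it.

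Third, the headline figure uses the 10.83% rate, which comes from a published trial that mixed benzodiazepine and non-benzodiazepine users. The inflation shrinks as the common rate rises and is gone at 50%.

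Two stronger readings are tempting, and the article supports neither. One is that the pooled analysis can only ever confirm a benefit. The second example in Step 4 shows the opposite: when the trial's own electroacupuncture rate exceeds 50%, pooling lowers it. The other is that the pilot was chosen because it agrees with the hypothesis. The Sample size section says it was run to assess feasibility and obtain a preliminary effect estimate, and nothing suggests selection on outcome. What can be said is that its result is known, non-randomised and the source of the planned rate.

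**Conclusion.** The planned pooling is a stated analysis rule that yields a non-randomised comparison, and it should be changed. The primary result is untouched, so this is a moderate point about one sensitivity analysis.

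The bias favours electroacupuncture when the trial's own electroacupuncture rate is below 50%. That covers a null effect at the protocol's own sham rate and an electroacupuncture rate lower than planned, which are the situations in which a robustness check matters most. In the null case the expected false difference is 8.0 percentage points, and a significant result favouring electroacupuncture becomes about five times as likely by chi-square (13.6/2.9 = 4.7).

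These figures assume simple pooling, the pilot fixed at 5/10, and 39 patients per arm with outcomes. The conclusion that the pilot cannot inform the electroacupuncture-versus-sham difference without bias needs only the absence of pilot controls.

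**What to change.** Delete the pooling sentence from Data management and its repetition in Study limitations, including the claim about testing different effect size assumptions. Report the pilot separately and descriptively; the article already refers to a supplementary appendix with the pilot results. State that robustness analyses use randomised participants only.

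Multiple imputation is already planned as such an analysis. A tipping-point analysis for missing discontinuation outcomes could be added.

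Removing the pooling costs nothing in patients, visits or data. The optional tipping-point analysis would take a little extra analysis work.

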### Statistical analysis

All statistical analyses will be conducted using SPSS version 28.0 (IBM Corp., Armonk, NY, United States) according to the intention-to-treat principle. A two-sided *p* < 0.05 will be considered statistically significant.

Continuous variables will be summarized as mean ± standard deviation or median (interquartile range), as appropriate. Categorical variables will be presented as frequencies and percentages. Between-group differences at single time points will be assessed using independent-samples *t*-tests or Mann–Whitney U tests for continuous variables and *χ*^2^ or Fisher’s exact tests for categorical variables.

Longitudinal outcomes will be analyzed using linear mixed-effects models with fixed effects for group, time, and group-by-time interaction, and random intercepts for participants. Missing data will be handled using likelihood-based estimation under the missing-at-random assumption. Multiple imputation will be conducted as a sensitivity analysis.

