#### Secondary outcome measures

Secondary outcomes are assessed at baseline, during treatment, and during follow-up. Detailed assessment procedures are provided in the Supplementary Appendix S1; assessment time points are summarized in Table 1.

(1) *Subjective Sleep Scales*

① Consensus Sleep Diary (CSD): Records total sleep time (TST), sleep onset latency (SOL), wake after sleep onset (WASO), sleep efficiency (SE), subjective sleep quality, and medication use (32–35).

② Insomnia Severity Index (ISI): 7-item scale (0–28) (36); scores ≥15 indicate clinically significant insomnia (37); a reduction of ≥8 points indicates meaningful improvement (38).

③ Pittsburgh Sleep Quality Index (PSQI): Global sleep quality (0–21); scores > 5 indicate poor sleep quality (39–42).

(2) *Daytime Functioning Assessment*

① Epworth Sleepiness Scale (ESS): Daytime sleepiness across eight situations (43, 44).

② Fatigue Severity Scale (FSS): 9-item scale (9–63); scores ≥36 indicate clinically significant fatigue (45–47).

③ Generalized Anxiety Disorder 7-item Scale (GAD-7): Anxiety severity (0–21) (48–50).

④ Patient Health Questionnaire-9 (PHQ-9): Depression symptom severity (51, 52).

(3) *Medication Reduction Response Assessment*

① NBZDs Reduction Rate

The NBZDs reduction rate was calculated using the following formula: NBZDs reduction rate = (Pre-treatment weekly NBZDs dose - Post-treatment weekly NBZDs dose) / Pre-treatment weekly NBZDs dose * 100% (Note: Pre-treatment refers to the baseline period, and post-treatment refers to week 6 of the treatment period) (16).

② Benzodiazepine Hypnotics Withdrawal Symptom Scale (BHWSS): 12-item self-report (3-point scale) assessing withdrawal symptoms (53, 54).

③ Medication Craving Visual Analogue Scale (VAS): 0–10 scale (0 = no craving, 10 = extreme craving) (55).

(4) *Objective sleep assessment parameters*

① Polysomnography (PSG): performed as the primary objective sleep assessment, with all participants undergoing one night of 8-h monitoring during screening to exclude other sleep disorders; sleep stages and parameters were manually scored according to the AASM Manual (Version 3.0) (56–58).

② Actigraph (ACT): Recorded for 7 consecutive days at baseline and at the end of intervention; parameters included number of awakenings (NOA), total wake time (TWT), sleep onset latency (SOL), total sleep time (TST), and sleep efficiency (SE) (59–62).

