### Efficacy evaluation criteria

① Primary Efficacy Outcome Measures

The primary efficacy outcome is the successful discontinuation rate of NBZDs at the end of the 6-week treatment period. Between-group differences in discontinuation rate will be evaluated using regression-based methods appropriate for binary outcomes.

② Secondary Efficacy Outcome Measures

a. Subjective Sleep Efficacy Evaluation

Subjective sleep outcomes, including the Insomnia Severity Index (ISI) and Pittsburgh Sleep Quality Index (PSQI), will be analyzed using longitudinal mixed-effects models incorporating repeated measurements across predefined study time points to estimate treatment effects over time.

b. Objective Sleep Efficacy Assessment

Objective sleep parameters derived from PSG and ACT will be analyzed using longitudinal mixed-effects models to account for within-subject correlation and to evaluate changes across study time points.

c. Daytime Functioning Assessment

Daytime functioning outcomes will be analyzed using longitudinal mixed-effects models to assess treatment effects across time.

d. NBZDs Reduction Response Evaluation

Medication reduction responses, including NBZDs reduction rate, withdrawal symptoms, and craving scores, will be evaluated using regression-based models appropriate to outcome type, with longitudinal modeling applied where repeated measurements are available.

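### The mixed model for secondary outcomes names no baseline adjustment, which costs precision, and its random-intercept covariance can misstate standard errors if correlation falls over the 10 weeks

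*Protocol article*

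**What the plan says.** The Statistical analysis section of the protocol article gives the model for longitudinal outcomes as "linear mixed-effects models with fixed effects for group, time, and group-by-time interaction, and random intercepts for participants". It mentions no baseline covariate, random slope, residual covariance structure or robust standard error.

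The Efficacy evaluation criteria section applies mixed models to the subjective scales as "longitudinal mixed-effects models incorporating repeated measurements across predefined study time points to estimate treatment effects over time", and to PSG and actigraphy as "longitudinal mixed-effects models to account for within-subject correlation and to evaluate changes across study time points". Daytime functioning is treated in the same way, as are withdrawal and craving where they are measured repeatedly. On timing, the Secondary outcome measures section states: "Secondary outcomes are assessed at baseline, during treatment, and during follow-up". Actigraphy is "Recorded for 7 consecutive days at baseline and at the end of intervention", and Table 1 shows the same two occasions for PSG.

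The primary outcome has its own analysis: "Between-group differences in discontinuation rate will be evaluated using regression-based methods appropriate for binary outcomes".

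**The concern.** Two features of the model matter.

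First, each outcome except BHWSS has a baseline value that the model does not use as a covariate. If baseline enters as one more response with its own free group difference, the group-by-time term subtracts the baseline in full instead of weighting it by its correlation with the later value. That is unbiased under randomisation but less precise, and with 39 per arm precision is scarce.

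Second, a random intercept with independent residuals makes every pair of visits equally correlated and every visit equally variable. For six measurements over 10 weeks of tapering this is restrictive. Baseline ISI is taken on medication and capped by the inclusion criteria, and participants then taper at different speeds because a dose step can be reversed. Weaker correlation between distant visits, or a growing spread, is plausible. In that case the reported confidence intervals would be too narrow at some visits and too wide at others. The article also relies on likelihood estimation under missing at random with 20% dropout planned, and that leans on a reasonable covariance model.

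**Working it through.** **Inputs from the article.** 39 per arm (Sample size); two-sided 0.05 (Statistical analysis). Visits from Table 1:
- ISI, CSD and VAS at weeks 0, 2, 4, 6, 8, 10
- PSQI, ESS, FSS, GAD-7 and PHQ-9 at weeks 0, 6, 10
- PSG and actigraphy at weeks 0 and 6
- BHWSS at weeks 2, 4, 6, 8, 10, with no baseline

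**Inputs assumed.** The article gives no SD, correlation or power for these outcomes, so there is no stated figure to reproduce. All correlations below are assumptions. Time is taken as categorical, residuals as independent and data as complete.

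**Step 1: is baseline a response?** The text does not say so outright. PSG and actigraphy have one post-baseline occasion each, so a longitudinal model of change is possible only if baseline is a response. For the other scales it is the natural reading.

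**Step 2: precision.** With equal variance s² at both visits and correlation rho, the change score has variance 2s²(1−rho) per participant and the baseline-adjusted value s²(1−rho²). The ratio is 2(1−rho)/(1−rho²) = 2/(1+rho).

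| rho | variance ratio | SE ratio |
|---|---|---|
| 0.3 | 1.54 | 1.24 |
| 0.5 | 1.33 | 1.15 |
| 0.7 | 1.18 | 1.08 |

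The loss shrinks if the spread grows. With rho = 0.5 and an SD 40% larger at follow-up, the ratio is (1 + 1.96 − 1.4)/(1.96 × 0.75) = 1.56/1.47 = 1.06, or 3% in SE. If the group difference at a visit is reported instead, baseline is not used at all. At equal variances the ratio is then 1/(1−rho²), which is 1.33 at rho = 0.5.

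**Step 3: standard errors.** Under equal variances the random-intercept model estimates one correlation, close to the average r of all visit pairs. For a change from baseline over k two-week steps, model SE / true SE = √[(1−r)/(1−rho_k)], and the type I error is 2[1−Φ(1.96 × ratio)].

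Six visits, AR(1) with correlation phi per two weeks. For phi = 0.8, r = (5×0.8 + 4×0.64 + 3×0.512 + 2×0.4096 + 0.3277)/15 = 0.616. At week 10, √(0.384/0.672) = 0.76.

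| phi | r | week 2: ratio (type I) | week 6 | week 10 |
|---|---|---|---|---|
| 0.9 | 0.789 | 1.45 (0.004) | 0.88 (0.083) | 0.72 (0.159) |
| 0.8 | 0.616 | 1.39 (0.007) | 0.89 (0.082) | 0.76 (0.139) |
| 0.7 | 0.476 | 1.32 (0.010) | 0.89 (0.080) | 0.79 (0.120) |

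A simulation agrees (phi 0.8, 39 per arm, no effect, 250 REML fits). The mean model SE was 0.197 at every visit, against empirical SDs of 0.151, 0.217 and 0.264 at weeks 2, 6 and 10. Rejection rates were 0.004, 0.072 and 0.144.

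**Step 4: other patterns.**
- AR(1) plus visit-specific noise (correlation c × phi^k, c = 0.6 to 0.8, phi = 0.7 to 0.9): week 10 type I error 0.08 to 0.10, week 6 0.06 to 0.07.
- Linear fall from 0.7 at two weeks to 0.4 at ten: 0.11 and 0.065. Fall only to 0.6: 0.074 and 0.056.
- Constant correlation and variance: ratio 1.00 at every visit.
- Visits at weeks 0, 6, 10 with phi 0.7 to 0.9: week 6 ratio 1.01 to 1.04; week 10 ratio 0.84 to 0.90 (type I error 0.08 to 0.10).
- PSG and actigraphy (two visits): ratio 1.00.
- Group difference at a visit: ratio 1.00 under any correlation pattern if variances are equal, but 0.88 at week 10 if the SD has grown by 40%.

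**The case against.** The strongest reply is that group, time, group-by-time and a random intercept is a standard, unbiased analysis of a randomised trial. On this view baseline covariates and residual covariance for secondary outcomes are commonly left to the analysis plan, which is not shown, and SPSS can add a residual structure to a random intercept. Much of this stands: nothing here is biased, and the article does not exclude a richer residual structure. But it does name the model terms and the random effect, so the point addresses a stated choice. The precision gain also uses data already collected.

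A reader might infer that standard errors at later visits will be too small. The documents do not support that. They give no correlation or SD and do not name the contrast to be reported. Under decay with equal variances the understatement concerns change-from-baseline contrasts with three or more visits, and the same assumption makes the week-2 test conservative. Pure AR(1) without measurement noise is also the unfavourable end for self-report scales.

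A reader might also take the sentence "Between-group differences at single time points will be assessed using independent-samples" to mean that t-tests give a second analysis of the same outcomes. That reading is strained. Longitudinal outcomes are assigned to the mixed model in a separate paragraph, and the t-test sentence fits baseline comparisons and measures taken once, such as the AES.

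**Conclusion.** The point holds in conditional form and for secondary outcomes only.

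- **Precision.** Without baseline adjustment, and with baseline as a response, the change contrast has 2/(1+rho) times the variance of an adjusted analysis. The SE is about 15% larger at rho = 0.5 and 8% larger at 0.7, assuming equal variances, and the loss is smaller if the spread grows. This part needs no assumption of decaying correlation and covers PSG and actigraphy too.
- **Standard errors.** If the residuals are independent and correlation falls with time, the six-visit outcomes (ISI, CSD, VAS) have week-10 type I error of roughly 0.08 to 0.16 and week-6 of about 0.06 to 0.09 for change contrasts, with early visits conservative. Very mild decay brings these near nominal. Scales at weeks 0, 6 and 10 are affected at week 10 only.

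The article has no stated power for a secondary outcome that this would undermine. It is a worthwhile, nearly free improvement; it does not invalidate the analysis.

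**What to change.** For the longitudinal secondary outcomes, model the post-baseline visits with fixed effects for group, visit and group-by-visit and the baseline value as covariate. Alternatively, keep baseline as a response and constrain the two arms to equal baseline means. Use an unstructured within-participant covariance and name a simpler fallback in advance, such as heterogeneous Toeplitz or AR(1), in case it does not converge. State which contrast is the main estimate, for example the group difference at week 6.

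For PSG and actigraphy this reduces to ANCOVA at week 6. BHWSS has no baseline in Table 1 and is modelled without its own baseline covariate. The primary analysis is unchanged.

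The cost is wording. Data and software stay the same, and the downside is a few more covariance parameters to estimate.
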